##### 2.6.3.2. Dance therapy

A customized dance therapy program with different types of dances can be developed in person or remotely depending on the hospital conditions during the COVID-19 pandemic.

### 2.7. Outcomes

#### 2.7.1. Efficacy evaluation

##### 2.7.1.1. Primary outcome

Considering the CONS, DISCEC, and FUSION groups, we will evaluate whether the decrease in the VAS score in the CP group is statistically significant compared to that in the corresponding control group on day 1 of hospitalization and 4 weeks after discharge.

##### 2.7.1.2. Secondary outcomes

For the CONS, DISCEC, and FUSION groups, we will evaluate whether the decrease in the VAS score of the CP group is statistically significant compared to that in the corresponding control group on day 1 of hospitalization and discharge.For the 3 treatment groups, we will evaluate whether the changes in the ODI, SF-36, and EQ-5D-3L scores in the CP group are statistically significant compared to those in the corresponding control group on day 1 of hospitalization and 4 weeks after discharge.For the 3 treatment groups, we will evaluate whether the changes in the ODI, SF-36, and EQ-5D-3L scores in the CP group are statistically significant compared to those in the corresponding control group on day 1 of admission and discharge.The average length of hospitalization will be compared between the CP group and the corresponding control group for all 3 treatment groups.After the patient is discharged from the hospital, a questionnaire for employee satisfaction will be used to evaluate the satisfaction of doctors, nurses, and hospital staff with the application of CP.After the patient is discharged from the hospital, the patient’s satisfaction with the medical services will be investigated through a questionnaire, and the satisfaction scores between the CP group and the corresponding control group will be compared.We will compare the consultation waiting time between the CP group and the corresponding control group.In addition to the fixed oral preparations and intravenous infusions, the amount of pro re nate (Pro Re Nate) analgesic used for pain will be investigated and compared between the CP group and the corresponding control group.The CP application rate and completion rate will be analyzed in the 3 groups.

#### 2.7.2. Economic feasibilty evaluation

##### 2.7.2.1. Cost-utility analysis

Using the EQ-5D score measured 4 weeks after discharge, we will compare the QALY value in each treatment group between the CP applied group and the CP non-applied group, and the medical expense in each group until 4 weeks after discharge will be calculated. We will conduct a cost-effectiveness analysis by calculating the ICER based on the difference in costs between the groups and the QALY value.

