## 2. Materials and methods

### 2.1. Study design

This single-center prospective observational study will be performed at Kyung Hee University Medicine Hospital and Kyung Hee University Korean Medicine Hospital to analyze the effectiveness, economy, and safety of using an integrated medical service CP in patients with L-HNP. The patients will be divided into groups that apply critical pathway of integrative medical services and those who do not.

From among the patients who agree to participate in the study, those who meet the inclusion criteria will be registered as research subjects. Among them, those who agree to participate in the integrated medical service CP will be assigned to the test group (integrated medical service CP applied group) and those who do not will be assigned to the control group (integrated medical service CP non-applied group). Both groups are further divided into a conservative treatment (CONS) group, an open discectomy (DISCEC) group, and an interbody fusion (FUSION) group based on the main medical treatment. In the test group, inpatient treatment will be administered according to the pathway of the prescribed protocol. In the control group, inpatient treatment will be administered based on the treating doctor’s judgment, without a prescribed pathway. The test group patients will be discharged after being hospitalized for a set hospitalization date, whereas in the control group, the time of discharge will be determined according to the judgment of the clinician. The study will be completed when the patients are evaluated during an outpatient visit to the Department of Neurosurgery of Kyung Hee Medical Center 4 weeks after discharge.

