##### 2.8.1.2. Secondary outcome analysis

The differences in VAS scores measured on day 1 of hospitalization and at 4 weeks after discharge in each treatment group will be analyzed with a linear model assuming a normal distribution. In the analysis model, including the treatment group (CP and control groups), age, sex, type of insurance related to back pain, region of residence, Charlson Comorbidity Index (CCI), surgery status, and hospitalization record as covariates and factors, we will evaluate if the VAS score reduction in the CP group is statistically significant compared to that in the control group. If the normality of the VAS scores is not satisfied, we will use a sandwich estimator or perform a nonparametric statistical analysis.The differences in VAS scores measured on the day of hospitalization and discharge in each treatment group will be analyzed with a linear model assuming a normal distribution. In the analysis model, including the treatment group (CP and control groups), age, sex, type of insurance related to back pain, region of residence, CCI, surgery status, and hospitalization record as covariates and factors, we will evaluate if the VAS score reduction in the CP group is statistically significant compared to that in the control group. If normality of the VAS scores is not satisfied, we will use a sandwich estimator or perform a nonparametric statistical analysis.The differences in ODI, SF-36, and EQ-5D-3L scores measured on day 1 of hospitalization and 4 weeks after discharge in each treatment group will be analyzed with a linear model assuming a normal distribution. In the analysis model, including the treatment group (CP and control groups), age, sex, type of insurance related to back pain, region of residence, CCI, surgery status, and hospitalization record as covariates and factors, we will evaluate if the VAS score reduction in the CP group is statistically significant compared to that in the control group. If normality of the ODI, SF-36, and EQ-5D-3L scores is not satisfied, we will use a sandwich estimator or perform a nonparametric statistical analysis.The differences in ODI, SF-36, and EQ-5D-3L scores measured on the day of hospitalization and discharge in each treatment group will be analyzed with a linear model assuming a normal distribution. In the analysis model, including the treatment group (CP and control groups), age, sex, type of insurance related to back pain, region of residence, CCI, surgery status, and hospitalization record as covariates and factors, we will evaluate if the VAS score reduction in the CP group is statistically significant compared to that in the control group. If normality of the ODI, SF-36, and EQ-5D-3L scores is not satisfied, we will use a sandwich estimator or perform a nonparametric statistical analysis.The average length of hospital stay in the CP group and control group will be compared by a 2-sample *t* test. If normality is not satisfied, the Wilcoxon rank-sum test will be performed.After patient discharge, we will perform the χ^2^ test or Fisher exact test for the test and control groups (CP applied and CP non-applied group) for staff satisfaction data obtained through a questionnaire.After patient discharge, we will perform a homogeneity test for the test and control groups (CP applied and CP non-applied groups) to evaluate patient satisfaction using the data obtained from the questionnaires.The consultation waiting time will be compared between the CP and control groups was compared using a 2-sample *t* test. If normality is not satisfied, the Wilcoxon rank-sum test will be performed.To compare the additional amount of pro re nate analgesic consumed between the CP and control groups, a 2-sample *t* test will be used. If normality is not satisfied in the normality test for additional analgesic use, the Wilcoxon rank-sum test will be performed.We will perform ANOVA (analysis of variance) to compare the average CP application and completion rates in the CONS, DISCEC, and FUSION groups of the CP group.

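### The cost-utility analysis bases the QALY on one EQ-5D score 4 weeks after discharge, without the day-1 and discharge scores that are also collected, and states no QALY period to match the costs

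*Protocol article*

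**What the plan says.** All references are to the protocol article.

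- **QALY input.** Section 2.7.2.1 (Cost-utility analysis) reads: "Using the EQ-5D score measured 4 weeks after discharge, we will compare the QALY value in each treatment group". No other EQ-5D time point, no formula and no period is given for the QALY.
- **Costs.** The same section says that "the medical expense in each group until 4 weeks after discharge will be calculated". The start of the period is not stated.
- **ICER.** It is obtained by "calculating the ICER based on the difference in costs between the groups and the QALY value".
- **EQ-5D-3L measurements.** Section 2.7.1.2 (Secondary outcomes) evaluates changes in the EQ-5D-3L score "compared to those in the corresponding control group on day 1 of admission and discharge". Section 2.8.1.2 (Secondary outcome analysis) also models "The differences in ODI, SF-36, and EQ-5D-3L scores measured on day 1 of hospitalization and 4 weeks after discharge". Three scores per patient are therefore planned: day 1, discharge, and 4 weeks after discharge.
- **Arms and discharge.** Sections 2.1 and 2.4 form the arms by the patient's willingness to follow the critical pathway (CP). For the CP arm, section 2.1 fixes the stay in advance: "The test group patients will be discharged after being hospitalized for a set hospitalization date". For controls it sets no such date and leaves the decision to the treating doctor: "in the control group, the time of discharge will be determined according to the judgment of the clinician". Length of stay is itself an outcome: "The average length of hospitalization will be compared between the CP group and the corresponding control group for all 3 treatment groups".

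**The concern.** A QALY is utility multiplied by the time spent at it. A single score at the end of follow-up leaves out how patients got there. An arm that recovers faster in hospital but ends at the same level gets no credit. An arm that pulls ahead only at the end is credited as if it had been ahead throughout.

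The single score also has no baseline. In a study without randomisation, the arms may differ in utility on day 1. Whatever part of that difference is still there at 4 weeks is then read as an effect of the pathway.

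The cost period is tied to discharge, and discharge is decided differently in the two arms. If stays differ, the arms are costed over periods of different length, and the text does not say that QALYs cover the same period as the costs.

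Economic feasibility is one of the three stated aims. Over a few weeks QALY differences are in the thousandths, and they form the denominator of the ICER. Small errors of definition can therefore change it a great deal.

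**Working it through.** **Plan's own figures.** The article gives no utility, QALY, stay or cost figure, so there is nothing of this kind to reproduce. Its sample size does reproduce: 2 × 1.12² × (0.84 + 1.96)² / 1.15² = 14.9, so 15 per group, and 17 with 10% dropout. It concerns the VAS and does not bear on this point.

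**Assumptions.** All utilities and stays below are assumed, to show how the methods behave. Costs and QALYs are taken to start at admission.

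**Formulas.** L is the stay in days; u0, ud and u4 are the utilities on day 1, at discharge and 4 weeks later.

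- Single score: u4 × days / 365, with 28 or L + 28 days. The article gives no multiplier, so both are shown.
- Area over the patient's own follow-up: [L(u0 + ud)/2 + 28(ud + u4)/2] / 365.
- Area over the first 28 days, for L up to 28: [L(u0 + ud)/2 + (28 − L)(ud + u28)/2] / 365, with u28 = ud + (u4 − ud)(28 − L)/28.

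**Step 1: a late gain, equal stays.** Both arms 0.40 on day 1 and 0.60 at discharge; 4-week score 0.80 (CP) and 0.75 (control); stay 7 days.

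- Single score: 0.05 × 28/365 = 0.0038, or 0.05 × 35/365 = 0.0048.
- Area: CP 7 × 0.50 + 28 × 0.70 = 23.1; control 7 × 0.50 + 28 × 0.675 = 22.4; difference 0.7/365 = 0.0019.
- The single score overstates the gain by a factor of 2 to 2.5. For the same cost difference its ICER is 50% to 40% of the area-based one.

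**Step 2: an early gain, equal stays.** Equal scores on day 1 and at 4 weeks; discharge score 0.70 (CP) and 0.60 (control); stay 7 days.

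- Single score: 0, so the ICER is undefined.
- Area: 0.5 × 0.10 × (7 + 28)/365 = 0.0048.

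**Step 3: baseline imbalance, no effect.** One arm is 0.05 higher at all three visits.

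- Single score: 0.0038 (28 days) or 0.0048 (35 days), all of it imbalance.
- Unadjusted area over 35 days: also 0.05 × 35/365 = 0.0048. The area alone does not cure this; adjustment for day-1 utility is needed as well.

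**Step 4: unequal stays.** Utilities as in step 1, with scores taken to attach to the visit whatever the day. Utility-days are shown as CP minus control.

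| Stay, CP / control (days) | Own follow-up | QALY difference | First 28 days | QALY difference |
|---|---|---|---|---|
| 7 / 7 | 23.1 − 22.4 | +0.0019 | 17.675 − 17.281 | +0.0011 |
| 7 / 10 | 23.1 − 23.9 | −0.0022 | 17.675 − 16.668 | +0.0028 |
| 7 / 14 | 23.1 − 25.9 | −0.0077 | 17.675 − 15.925 | +0.0048 |
| 10 / 7 | 24.6 − 22.4 | +0.0060 | 16.957 − 17.281 | −0.0009 |

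Over own follow-up, the arm that stays longer gains utility-days simply because it is followed longer. Over a common period this does not happen. The table shows what would follow if QALYs were accumulated over stay plus 28 days; the article does not say that they will be.

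**The case against.** **The wording may only name the last visit.** Section 2.7.2.1 is two sentences and does not exclude other scores. Section 2.7.2.2 likewise names only the 4-week VAS, although it must use day 1. The QALY formula may sit in a fuller document. This has some force, but the two sections differ: 2.7.2.2 speaks of a reduction, which implies a baseline, and 2.7.2.1 does not. The article does not leave the utility input open; it names one time point. Followed as written, that is the wrong input.

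**The window effect is not established.** A lone score has no time window, and the article states no QALY period. The sign reversals in step 4 therefore belong to one possible reading. This stands. What the text does support is narrower: the cost period depends on the stay, and no QALY period is stated to match it. Extra inpatient days are real costs and belong in the comparison.

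**The figures are assumed.** This stands too. The article shows that stays may differ, not that they do, nor in which direction.

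**Stronger readings.** A reader might infer that the ICER will be wrong or have the wrong sign. The documents do not support that: if baselines, recovery paths and stays happen to match, the bias could be small. A reader might also extend the point to the VAS-based ICER in section 2.7.2.2. It uses the same cost period, but a VAS reduction does not accumulate over time, and no figure supports a distortion there.

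**Conclusion.** Wrong as written. The stated QALY input is a single end-point EQ-5D score, although three scores are collected. It ignores the utility path and, with arms formed by preference, lets a persisting day-1 difference into the ICER. Complete data would not remove either problem.

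The size and direction cannot be derived from the documents. With the assumed utilities and equal 7-day stays, the single score is 2 to 2.5 times the area-based difference in one case, and zero against 0.0048 in another.

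The second part is conditional: if stays differ by arm, the cost periods differ, and the QALY period is not stated to match. This takes admission as the start of costs, which the article does not say. The point concerns a stated aim of the study, not its primary outcome.

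**What to change.** Reword section 2.7.2.1 as follows.

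1. Compute each patient's QALY as the area under the day-1, discharge and 4-week EQ-5D-3L utilities, using the actual days between visits.
2. Compare the arms within each treatment group with adjustment for day-1 utility and the covariates already listed in section 2.8.1.2.
3. Count QALYs and costs over the same period, and state its start and end.
4. As the main or a sensitivity analysis, use a common window from admission that lies inside every patient's follow-up, for example the first 28 days, interpolating utility at day 28. Every patient who attends the visit 4 weeks after discharge has been followed for at least that long.

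**Cost.** No new visit or questionnaire is needed. Costs must be datable so that they can be cut at the end of the window; the article does not say whether they are. A common window drops some late observed days. A longer one, reaching the last visit of the patients with the longest stays, would need extrapolated utilities and also costs after the 4-week visit, which are not collected.

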In addition to the existing cooperation system between WM and KM, integrated medical services provide comprehensive medical services to patients through complementary and alternative medicine (CAM), the safety and effectiveness of which have been verified in areas where conventional medicine has limitations (mainly mental, spiritual, and social health).^[7]^ Recently, the Ministry of Health and Welfare conducted an integrated medical research support project to prepare a model of integrated medical care, a new medical paradigm in which WM and KM doctors develop integrated diagnosis and treatment technologies with equal qualifications, encompassing various complementary and alternative medicine techniques.^[8]^

The critical pathway (CP) is a tool that lists the interventions of doctors, nurses, and other medical personnel over time to standardize the contents of medical interventions to be applied and maximize efficiency while minimizing medical costs within a fixed hospitalization period.^[9–11]^ After CP was first applied in the medical environment in the United States in the 1990s, it has been applied in clinical settings in Korea since the late 1990s. Recently, there has been a growing movement to introduce and apply CP in the clinical field of KM to improve the quality of medical care and patient satisfaction with medical services.

To date, CP has been studied in WM^[12,13]^ and KM^[14]^ for L-HNP, a commonly encountered disease in both WM and KM contributing to the economic burden. Although there have been studies on CP based on collaboration between WM and KM for patients with acute pain after lumbar spine surgery,^[15]^ there have been no studies on an integrated medical service CP.

An integrated medical service CP encompassing WM, KM, and CAM for L-HNP has been developed at the Department of Neurosurgery and Korean Rehabilitation Medicine at Kyung Hee Medical Center. However, further research is necessary before its clinical application.

In this study, patients with L-HNP were divided into groups that received integrated medical service CP and those that did not. They were prospectively observed to analyze and compare the effectiveness, economic feasibility, and safety of the CP.

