### 2.4. Clinical trial plan and critical pathway schedule

Among patients with lumbar intervertebral disc herniation visiting the Neurosurgery outpatient department of Kyung Hee Medical Center, patients with a VAS score of 7 or higher who require hospitalization can consent to participate in this study. Following patient consent, the doctors and research nurses will screen the patients according to the inclusion and exclusion criteria, enroll those who pass the screening, and confirm the participants intention to receive treatment using an integrated medical service CP. Depending on their intention to participate in the CP application, participants will be classified into the test or control group. Upon admission, the patients will be assigned to the CONS group, DISCEC group, and FUSION groups according to the judgment of the medical staff. The test group will receive inpatient treatment according to a previously developed integrated medical service CP plan, and the control group will receive inpatient treatment according to the clinician’s judgment without a set protocol. The study will be deemed complete when all patients will be evaluated during an outpatient visit to the Neurosurgery Department of Kyung Hee Medical Center 4 weeks after discharge.

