#### 2.5.1. Average change in the VAS score

The average change in VAS was calculated as 2.27 to 6.14 = −3.87 in the treatment group and 3.37 to 6.09 = −2.72 in the control group. Therefore, the difference in the change in the VAS score before and after treatment between the 2 groups was d=−3.87 to (−2.72) = −1.15.

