#### 2.5.2. Variance in the change in the VAS score

Assuming that the correlation coefficient (ρ) for pre- and posttreatment was 0.5, the variance in the VAS score change before and after treatment for the treatment and control groups was calculated as follows:

Treatment group: Var(A−B)=Var(A)+Var(B)−2ρSD(A)SD(B)$=1.29^{2}+0.84^{2}-2*0.5*1.29*0.84\approx 1.13^{2}$

Control group: Var(A−B)=Var(A)+Var(B)−2ρSD(A)SD(B)$=1.21^{2}+0.93^{2}-2*0.5*1.21*0.93\approx 1.10^{2}$

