#### 2.5.4. Calculation of the number of subjects

Assuming that the significance level (α) is 5% and the test power (1-β) is 80%, the number of subjects in each group is calculated so that the ratio of the 2 groups is 1:1.

$$\begin{array}{l} n=\frac{2\sigma^{2}{\left(Z_{1-\beta }+Z_{1-\frac{\alpha }{2}}\right)}^{2}}{d^{2}}=\frac{2\times 1.12^{2}{\left(Z_{0.8}+Z_{0.975}\right)}^{2}}{{\left(-1.15\right)}^{2}}\approx 15 \end{array}$$

The CP group is divided into the CONS, DISCEC, and FUSION groups, and CP non-applied group is also divided into the corresponding 3 groups. The minimum number of subjects required for this study is 15 per group, with a total of 90; however, considering the dropout rate (10%), a total of 102 subjects (17 per group) will be enrolled.

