##### 2.7.2.2. Cost-effectiveness analysis

The VAS score will be measured 4 weeks after discharge to determine the reduction in the VAS score in each CP applied and non-applied group, and the medical expense in each group until 4 weeks after discharge will be calculated. A cost-effectiveness analysis will be performed by calculating the ICER based on the difference in costs between the groups and the reduction in the VAS score.

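### Both economic analyses end in a point ICER per stratum, a ratio that cannot be ranked when negative and is unstable for QALYs at about 15 patients per arm (minor)

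*Protocol article*

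**What the plan says.** Section 2.7.2 holds two economic analyses. In section 2.7.2.1, QALYs derived from the EQ-5D at 4 weeks after discharge are compared between pathway and control within each treatment group, and medical expense to the same time point is calculated per group. It concludes: "We will conduct a cost-effectiveness analysis by calculating the ICER based on the difference in costs between the groups and the QALY value". Section 2.7.2.2 determines VAS reduction and expense per group and likewise ends by "calculating the ICER based on the difference in costs between the groups and the reduction in the VAS score".

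Section 2.8 covers efficacy and safety and has no economic subsection. The ICER is therefore the only economic summary measure the article names, although economic feasibility is one of its three objectives. The Introduction describes critical pathways in general as a tool to "maximize efficiency while minimizing medical costs within a fixed hospitalization period".

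The sample size in section 2.5 rests on VAS alone. No effect or SD is given for EQ-5D, QALYs or cost.

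**The concern.** An ICER is a cost difference divided by an effect difference. It reads well when both are positive (dearer and better). It reads badly in two other situations.

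- **Cheaper and better.** The ratio is negative. The same negative value arises when the pathway is dearer and worse. For a fixed saving, a larger benefit moves the ratio towards zero, so its size does not order results by merit.
- **Small or imprecise denominator.** When the effect difference is small relative to its standard error, the ratio swings widely. Chance can then put the denominator on the wrong side of zero, which reverses what the ratio appears to say.

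At stake is the summary statement for the economic objective in each of the three treatment strata. The primary outcome is not affected.

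**Working it through.** **Inputs from the article.** Planned difference in VAS change: "between the 2 groups was d=−3.87 to (−2.72) = −1.15" (section 2.5.1). Pooled SD 1.12 (section 2.5.3), which relies on an assumed pre/post correlation of 0.5 (section 2.5.2). Two-sided 5% level, 80% power, 1:1 ratio, 15 evaluable and 17 enrolled per group (section 2.5.4).

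**Inputs assumed here.** Utility difference 0.05 with SD 0.15 to 0.30, because the article gives neither. I take the QALY difference to have the sign of the utility difference. I also read both ICERs as formed within stratum. Section 2.7.2.1 says so; section 2.7.2.2 is less explicit.

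**1. The plan's own figure.** n = 2 × 1.12² × (0.8416 + 1.9600)² / 1.15² = 14.89, so 15 per group. Allowing for 10% dropout, 15 / 0.9 = 16.7, so 17, and 6 × 17 = 102. The stated sizes reproduce.

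**2. Negative ratios do not rank (illustration).** Take a saving of 100 cost units. With an extra VAS reduction of 1.15, the ICER is −100 / 1.15 = −87. With twice the benefit, it is −100 / 2.30 = −43. The better result has the ratio nearer zero. A pathway dearer by 100 and worse by 1.15 gives 100 / (−1.15) = −87, the same as the first case.

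**3. VAS denominator: wrong sign.** At 15 per arm, SE = 1.12 × √(2/15) = 0.409. P(wrong sign) = Φ(−1.15 / 0.409) = Φ(−2.81) = 0.25%.

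**4. VAS ICER: unbounded interval.** A 95% Fieller set for a ratio is bounded only when the denominator differs from zero at the two-sided 5% level. P(unbounded) is therefore 1 minus the power for the effect difference.

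| Evaluable per arm | Power (noncentral t) | Unbounded, one stratum | At least one of three strata |
|---|---|---|---|
| 15 | 77.5% | 22.5% | 1 − 0.775³ = 53.5% |
| 17 | 82.7% | 17.3% | 1 − 0.827³ = 43.4% |

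The normal approximation gives 19.7% and 15.1% per stratum. A simulation of 200,000 runs gives 22.5% and 17.3%, agreeing with the t figures. The last column assumes independent strata.

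**5. QALY denominator: wrong sign, 15 per arm.** P = Φ(−0.05 / (SD × √(2/15))).

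| Assumed utility SD | SE | P(wrong sign) |
|---|---|---|
| 0.15 | 0.055 | 18% |
| 0.20 | 0.073 | 25% |
| 0.30 | 0.110 | 32% |

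With SD 0.20, equal true costs, and cost and effect differences taken as independent, half of the ICERs are negative. Of all ICERs, 0.5 × 0.247 = 12% are dearer and worse, which is about one negative ICER in four.

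**The case against.** Four parts of the opposing case stand.

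- **The components are there.** QALYs, VAS reduction and expense are all obtained per group, so a careful reader can find both differences and see the quadrant. A reader might infer that a favourable economic result would be uninterpretable; the article does not support that.
- **No interval is promised.** The article plans no confidence interval for the ICER. The interval method, dominance rule and threshold range are commonly left to the full protocol or analysis plan, which is not shown. Their absence is not an error, and the Fieller figures only measure how unstable the ratio is.
- **The VAS ambiguity is almost nil under the planned effect.** If costs are equal, 0.25% of negative VAS ICERs are dearer and worse. Assuming a 10% saving and a cost coefficient of variation of 0.3 to 0.5, the share is 0.05% to 0.10%. A negative VAS ICER would nearly always mean that the pathway dominates. It is also tempting to say that one stratum in four lacks a bounded interval. The plan's inputs give less, and the figure cannot be carried to the QALY ICER, which has no planned effect.
- **Cost saving is not a stated hypothesis of this trial.** The sentence in the Introduction defines critical pathways in general. This pathway also includes diet and dance therapy, so dearer but better, where an ICER reads normally, is equally open.

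It is also true that net benefit adds no information: a wrong-sign effect estimate would pull it down too. Net benefit is linear in both differences, however, so its value and interval stay defined and ordered in every quadrant. What survives is narrower: the one summary measure that the article names, twice, is a ratio that works in only part of the plausible range.

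**Conclusion.** The concern holds as a minor point about the choice of summary measure. The ICER is the only one named, its size does not rank results when negative, and at about 15 patients per arm it can be unstable.

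The weight falls on the QALY ICER, where the wrong-sign risk is 18% to 32% per stratum. That range rests wholly on the assumed utility difference of 0.05 and SD of 0.15 to 0.30. For the VAS ICER the sign is secure under the planned effect (0.25% wrong), and the remaining weakness is imprecision: 22.5% of strata with an unbounded 95% Fieller set at 15 per arm, 17.3% at 17. Those figures rest on the planned difference, the assumed correlation of 0.5 and equal arms. Equal arms are not assured, since the groups form by patient choice: "Depending on their intention to participate in the CP application, participants will be classified into the test or control group".

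**What to change.** In section 2.7.2, or the economic part of the analysis plan:

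1. For both analyses, report incremental cost and incremental effect separately, each with a 95% interval (for example bootstrap), and name the quadrant.
2. For the QALY analysis, make incremental net monetary benefit the decision quantity: λ × (QALY difference) − (cost difference), over a stated range of λ, with an interval or an acceptability curve.
3. Quote an ICER only when both differences have the same sign, and state dominance otherwise.
4. For the VAS analysis, the separate increments and the quadrant suffice. The article gives no willingness to pay per VAS point, so net benefit over a range of λ is optional there.

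I would not require the full covariate list of section 2.8.1.2 in these models: seven covariates plus treatment on about 30 patients per stratum is debatable.

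The cost is some wording and a few lines of code, using data already collected. The downside is that a range of λ must be stated and the single headline ratio loses prominence.
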